# Statistical analysis

Randomization will occur using blocked randomization (1:1) and will be conducted using double-observed coin-toss. In the event that the coin should fall, the face up side will be considered the allocation. Heads active, tails control. Participants will not be allocated to any group prior to sequence generation. All analyses will be performed by [name] PhD, a statistician, under blinded conditions. The sample size estimates indicate that a sample of about 36 in each group will be adequate to detect a 10% change in the primary outcome of self-reported pain assuming an intrapatient variability of 15%, a two-sided significance level of 5%, and a power of 80%.

All data will be analyzed according to intention to treat. We will calculate the mean change scores between groups at the specific weeks and the primary endpoint of change from base line to week 12. For any missing data at week 12, we will use LOCF at week 8. Paired t-tests will assess within group changes and two-sample t-tests will compare between groups. All p-values will be exact.

Participants

According to the sample size calculations, 75 participants, randomly allocated to treatment and control group, will take part in this study. Participants will be Canada Post employees, and CUPW union members. Most will be from Mississaugas' Gateway Processing Centre, with a minority coming from Canada Post centers from the surrounding area. Their job function will be varied, ranging from sorting workers to letter carriers. The age range will be workers from 18 to 65 years old.

Recruitment:

Recruitment for the study will be facilitated by Canada Post Corporation and CUPW representatives. Posters and information sheets will be posted and distributed throughout eligible sites. Interested parties will be encouraged to contact the clinicians directly, either by phone or e-mail and provide their name, phone number, and mailing address. Interested participants will be mailed a Participants Information Kit which will include: a sample consent form, a Backgrounder explaining the purpose of the pilot, a description of Naturopathic Modalities, a question and answer sheet regarding the study, contact list and phone numbers of Naturopathic Doctors, Canada Post, and CUPW representatives, Naturopathic Doctors business cards. Interested participants will be encouraged to ask questions to their Canada Post, CUPW, and Naturopathic Doctors. Interested participants will be contacted by phone, and scheduled for a 1 hour initial consultation in a designated room at the Canada Post Gateway Processing Plant. At this consultation, any outstanding questions will be answered by the Naturopathic Doctors, a consent form will be signed and witnessed, and the intake interview and physical exam will take place. Eligible participants will be randomly assigned to either the control or treatment groups, and will be contacted by telephone regarding further appointment times.

Choosing to withdraw will terminate any further study treatment. Withdrawal will not carry any negative consequences towards the participant from the Naturopathic Clinicians, CUPW or Canada Post Corporation. Participants in the control group that choose to begin treatment will be offered to begin treatment at the conclusion of the trial and we will follow them for an additional 4 weeks.

Risks:

Acupuncture carries with it a minimal risk of infection or organ perforation. All attempts will be made by the Naturopathic Doctors to ensure proper sterile and clean field acupuncture techniques, as specified in the BDDT acupuncture guidelines. Acupuncture points near organs which may be perforated will not be needled. Proper exercise procedures will be initially explained and demonstrated to the patient, but there remains a chance that improper exercise use may harm the patient.

Proper sterile acupuncture technique, as specified in the BDDT acupuncture guidelines, will be used. During the initial visit, potential subjects will be screened for risk factors. Patients will be provided with Naturopathic Doctors contact information, and will be encouraged to contact them with any questions, concerns, or emergencies. To minimize the risk of fainting associated with acupuncture, patients will be treated in a prone position.

Possible Benefits:

Participants may benefit by gaining permanent or temporary relief from their chronic back pain. They will gain an understanding of the process of research, by being active participants in it. The information provided by this study will allow for a better understainding of the role of Naturopathic Medicine in the workplace, and may lay the foundation for an in-depth evaluation of the cost / benefit analysis of Naturopathic Medicine in the work place.

The Consent Process:

[name] or [name] will telephone each person who volunteers to participate in the study to introduce him/herself, explain the purpose and scope of the study, and assure each individual of anonymity, both during the study and in published reports. The potential participants will be assured that they can stop participating in the study at any time without penalty. At the conclusion of the telephone call, arrangements will be made to mail the Participants Information Kit to interested parties. The kit will contain a sample consent form, Background information on the project, a description of Naturopathic Modalities, Question and Answer sheet, Contact list and phone numbers, and Naturopathic Doctors business cards. When provided with the study packet, they will be asked to read the material, and then direct any questions to either their CUPW or Canada Post representative, or Naturopathic Doctor. Interested parties will be asked to come for a 1 hour asessment visit at the Gateway site, which will first answer any further questions, and then sign the consent form if they still wish to participate in the study.

Confidentiality:

All patients will be assigned a unique number during the intial visit, all analysis will be performed using the patients assigned number. The records and questionnaires will be kept in a locked filing cabinet and shared only with study personnel. The records and questionnaires will be kept at CCNM for 25 years unless a patient requests otherwise.

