Interim for the control groups (Visit 2 – Day 7, Visit 3 – Day 21, Visit 4 – Day 35, Visit 5 – Day49, Visit 6 – Day 63, Visit 7 – Day 77, Visit 8 – Day 91)

End of Treatment (Visit 25 - Day 91), Questionnaires and Medication diaries filled in for the last time

Follow-up data will be collected at 6 months post treatment via a mailed questionnaire package containing the Oswestry, Roland and Morris, and SF-36 questionnaires, Perceived Benefit of Treatment scales, as well as the pain killer and adjunctive back pain treatment chart. Non-responders will receive reminders by post. If this is unsuccessful, the patients will be telephoned.

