# Outcomes

Our primary outcome is self-reported low back pain measured by the Oswestry Low Back Pain Disability Questionnaire, and Quality of Life (SF 36). The Oswestry questionnaire characterizes the extent to which low back pain impacts on the participant’s life, work, and daily function and is scored from 0 to 50, or 0% to 100%. The higher the score, the more the low back pain affects life: 0% (no disability) to 100% (totally disabledor bed ridden). The SF-36 questionnaire aims to assess the degree to which specific quality of life measurements are affected by a course of treatment. The higher score indicates improvement in the particular quality of life category.

Secondary outcomes assessed will included self reported pain scale, the Roland Morris Disability questionnaire, forward lumbar flexion range of motion, weight, body mass index (BMI), use of non-steroidal anti-inflammatory Drugs (NSAIDS) and use paramedical interventions. All measures will be assessed at baseline, weeks 4, 8 and 12. We will assess the construct validity of the Oswestry with the the Roland Morris Disability questionnaire and assume good correlation (>0.5). We will ask for self-reported adherence to the regimen, adverse events, and perceived benefit (Naturopathic care group only) at the same time periods.

Adherence with treatment will be monitored on a semi-weekly basis using a percentage compliance scale, with <70% adherence considered non-compliant at each time point. This is a strategy we previously assessed in the HIV/AIDS field.

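### Week-8 LOCF is the only method fixed for missing week-12 data; it assumes no late change, can bias the primary comparison either way, and leaves earlier losses undefined

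*Protocol*

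**What the plan says.** The Statistical analysis section of the protocol sets the principle, "All data will be analyzed according to intention to treat", and names "the primary endpoint of change from base line to week 12". It says that "two-sample t-tests will compare between groups", and it gives one rule for gaps: "For any missing data at week 12, we will use LOCF at week 8". It names no second method and no sensitivity analysis for missing data.

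The Outcomes section says: "All measures will be assessed at baseline, weeks 4, 8 and 12". A week-4 value is therefore planned for everyone, but the missing-data rule does not mention it.

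For the mailed 6-month follow-up the protocol adds: "Non-responders will receive reminders by post. If this is unsuccessful, the patients will be telephoned". No similar step is written for a missed week-12 form. The Recruitment section says that withdrawal ends study treatment and does not say whether outcome forms continue to week 12.

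**The concern.** Carrying week 8 forward treats a value taken four weeks early as the week-12 result. The intervention arm has two treatments a week for 12 weeks, so 2 x 4 = 8 of its 24 treatments are scheduled after week 8. Assuming a frozen outcome over that stretch is hard to defend. The t-test then handles filled values as if they had been measured, so no allowance is made for the uncertainty of filling.

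The two arms may well lose people at different rates. The intervention arm has 25 listed visits and the control arm 8, which could mean more loss under the heavier schedule. Controls receive a booklet and encouragement, which could mean more loss among them. The protocol does not settle which, so the direction of any bias cannot be known beforehand.

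A second gap concerns people who miss both week 8 and week 12. The rule gives them no source value, and a t-test on change to week 12 needs one. Two analysts could read the sentence differently and produce different primary analysis sets.

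**Working it through.** **Inputs from the protocol (Statistical analysis and Participants sections).** The difference is 10 points ("adequate to detect a 10% change in the primary outcome of self-reported pain"). The SD is 15 points ("assuming an intrapatient variability of 15" per cent). The test is two-sided at 5% with 80% power, about 36 per group, 75 participants in all, allocated 1:1. Reading the 15 as the between-person SD in each arm is an assumption; it is the reading that reproduces the stated sample size.

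**The plan's own figure.** n per group = 2 x (1.960 + 0.842)^2 x (15/10)^2 = 35.3, rounded up to 36. The stated figure reproduces, and the sample size is not at issue here. The 75 planned exceed 2 x 36 = 72 by 3, so 3/75 = 4% loss is covered.

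**Bias with no true effect.** If both arms have the same late change, then

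false difference = (share carried in one arm - share carried in the other) x change from week 8 to week 12.

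The dropout shares and time courses below are assumptions, because the protocol gives none.

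- *Milder case.* Both arms improve 10 points linearly over 12 weeks, so the change after week 8 is 10 x 4/12 = 3.33 points. With 30% and 10% carried: (0.30 - 0.10) x 3.33 = 0.67 points.
- *Extreme case.* Both arms improve 6 of 10 points after week 8. With 25% and 4% carried: (0.25 - 0.04) x 6 = 1.26 points.

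The arm with more carried values looks worse. Swapping the shares between arms reverses the sign.

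**Type I error.** With 37.5 per arm, the standard error of the difference is 15 x sqrt(2/37.5) = 3.46 points. The false difference divided by this is the non-centrality of the t-test (73 df):

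| Case | False difference | Non-centrality | Rejection rate |
|---|---|---|---|
| Milder | 0.67 | 0.19 | 5.4% |
| Extreme | 1.26 | 0.36 | 6.5% |

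If 15 is instead the SD at each visit and the within-patient correlation is 0.6, the SD of change is 15 x sqrt(2 x 0.4) = 13.4 and the extreme case gives about 6.9%. A fair summary of that case is about 6.7%.

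**Bias with a true 10-point difference at week 12, equal dropout.** Expected LOCF difference = (1 - q) x 10 + q x (week-8 difference), where q is the share lost between weeks 8 and 12.

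| q | Week-8 difference 6.67 (linear growth) | Week-8 difference 12 (early peak) |
|---|---|---|
| 5% | 9.83 | 10.1 |
| 10% | 9.67 | 10.2 |
| 20% | 9.33 | 10.4 |
| 30% | 9.00 | 10.6 |

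The shift runs from -1.0 to +0.6 points, so LOCF is not reliably conservative even with equal dropout.

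**Power if people without a week-8 value fell out of the t-test.** This applies on that reading only. By non-central t, for 10 points and SD 15:

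- no loss: 75/2 = 37.5 per arm, power 81%
- 10% loss: 75 x 0.90/2 = 33.75 per arm, power 77%
- 15% loss: 75 x 0.85/2 = 31.9 per arm, power 75%

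**The case against.** The strongest defence is that the effects are small. The extreme case puts 60% of all improvement into the last four weeks and makes carry-forward about six times as common in one arm (25/4). Even then the type I error stays below 7%. It also assumes more loss in the control arm, while visit burden points to more loss in the intervention arm. With improving participants, that would bias against the intervention. All of this stands. It limits the size of the point and rules out claiming a direction.

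A reader might infer that the plan drops everyone lost before week 8 and so contradicts its own intention-to-treat statement. The text does not support that. It orders no exclusion, and LOCF applied to any missing week-12 value could also mean carrying week 4 or baseline forward. LOCF itself keeps people in their randomised arm. What remains is an undefined case.

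A reader might also infer that week-12 non-responders will not be chased, or that withdrawal ends outcome collection. The protocol is silent on both. The week-12 forms are due at a clinic visit, whereas the reminders belong to a mailed package. These are omissions and are not counted as errors.

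Finally, an analysis plan that is not shown might add detail. That does not remove the point, because the protocol itself fixes the method for the primary endpoint.

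**Conclusion.** The concern holds in a limited form. Week-8 LOCF is a weak sole method for the primary endpoint, and a better one is available from data already planned. Under assumed dropout and time courses, the false difference is about 0.67 points (type I error 5.4%) in a milder case and about 1.3 points (about 6.7%) in an extreme one, in either direction. These sizes rest on an SD of 15 points, 37.5 per arm and dropout figures that the protocol does not supply.

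The handling of participants missing both week 8 and week 12 is left open. The power figures of about 77% and 75% apply only if such people were left out. The change should be made, but the point does not by itself invalidate the trial.

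**What to change.** Replace LOCF as the primary method with a mixed model for repeated measures on the Oswestry at weeks 4, 8 and 12. Include arm, visit, arm-by-visit and baseline score, and take the week-12 difference between arms as the primary estimate. Include every randomised participant with any post-baseline form, in the randomised arm. This settles how someone last seen at week 4 enters the analysis. State that people with no post-baseline form contribute nothing to the model, and report their number by arm.

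Keep LOCF as a sensitivity analysis, and say which value is carried when week 8 is also missing.

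It would also help, though it is not essential to this point, to say that week 4, 8 and 12 forms are still sought from people who stop study treatment, and to use the mail-then-telephone reminder for a missed week-12 form.

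The cost is a change of wording, slightly more analysis work and, if the reminders are extended, a few mailings and calls. The model assumes that data are missing at random. Comparing it with LOCF, which rests on a different assumption, shows how far the conclusion depends on that.

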At the first visit, prior to any treatments, the Oswestry, Roland and Morris, and SF-36 questionnaires will be completed by the patient to assess baseline. The Pain Medication and Pain Therapies diary will be collected. Both treatment and control groups will receive The Back Booklet, and patients will be instructed to follow the treatments as instructed in the booklet. On subsequent visits, the control group patients will be questioned on the performance of the Book Exercises, and will be encouraged to continue performing them.

The treatment group patients will be positioned prone, and specific acupuncture treatment for low back pain will be applied. During the acupuncture treatment, data on patients’ lifestyle and diet will be obtained, and diaphragmatic deep breathing exercises will be performed. On subsequent visits, the treatment group will continuously receive acupuncture treatment, receive lifestyle and diet counseling, continue to perform deep breathing relaxation techniques, and be encouraged to continue with the exercises as instructed in the exercise booklet.

Intervention arm patients will attend two treatments per week, for a total of 24 treatments over the period of 12 weeks. Control arm patients will receive one initial session with a Naturopathic Doctor, who will give them general advice and exercises as specified in the booklet, and will have bi-weekly visits with the Naturopathic Doctor who will question them on the performance of the Book Exercises, and will encourage the patient to continue performing them.

Both the Intervention and Control arm will complete the Oswestry, Roland and Morris, SF-36, and Perceived Benefit of Treatment questionnaires at 4, 8, and 12 weeks during the study. Both groups will also hand in the Pain Medication and Treatment diary chart, and exercise log at every visit.

Study period is 12 weeks. Clinical evaluations will be performed at:

Baseline (Visit 1 - Day 1)

Interim for the treatment groups: (Visit 2 - Day 7, Visit 3- Day 10, Visit 4 – Day 14, Visit 4 – Day 17, Visit 5 – Day 21, Visit 6 – Day 24, Visit 7 – Day 28, Visit 8 – Day 31, Visit 9 – Day 35, Visit 10 – Day 38, Visit 11 – Day 42, Visit 12 – Day 45, Visit 13 – Day 49, Visit 14 – Day 52, Visit 15 – Day 56, Visit 16 – Day 59, Visit 17 – Day 63, Visit 18 – Day 66, Visit 19 – Day 70, Visit 20 – Day 74, Visit 21 – Day 77, Visit 22 – Day 81, Visit 23 – Day 84, Visit 24 – Day 88, Visit 25 - 91) ie. Monday and Thursday, or Tuesday and Friday.

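### The t-test on change from baseline is valid, but ANCOVA on the baseline already collected would generally be more precise at no cost

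*Protocol*

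**What the plan says.** The Statistical analysis section of the protocol defines the comparison in two sentences. The first sets the endpoint: "We will calculate the mean change scores between groups at the specific weeks and the primary endpoint of change from base line to week 12". The second sets the tests: "Paired t-tests will assess within group changes and two-sample t-tests will compare between groups". No covariate, ANCOVA or other adjusted model appears anywhere in the protocol.

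The baseline values are available for adjustment. In its description of the first visit, the Methodology section has patients fill in the Oswestry, Roland-Morris and SF-36 forms before treatment starts. The Outcomes section adds that all measures are taken at baseline and at weeks 4, 8 and 12.

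The sample size statement in the Statistical analysis section is that "a sample of about 36 in each group will be adequate to detect a 10% change in the primary outcome of self-reported pain", at a two-sided 5% level and with 80% power. Its variability input is given only as "assuming an intrapatient variability of 15" per cent. It does not say whether this is the SD of the change score, the SD at one time point, or the within-patient SD.

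**The concern.** A change score subtracts the whole baseline value, which amounts to a regression with the baseline slope set to 1. If the true slope is below 1, too much baseline is subtracted. Two things follow.

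- The comparison carries variance that an estimated slope would remove.
- If the arms differ at baseline by chance, the change-score estimate is shifted, conditional on that imbalance, by (1 − slope) times the difference. With about 37 per arm, such imbalances are not rare.

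At stake is precision in a small trial with little reserve: the Participants section plans 75 people, three more than 2 × 36.

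A lesser matter is that the protocol plans paired t-tests within arms without saying what they are for. Participants enter with back pain of more than 6 weeks, and both arms receive the booklet and its exercises. Improvement within either arm can therefore reflect natural recovery, regression to the mean or the shared advice, and a within-arm p-value cannot separate these from the effect of naturopathic care.

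**Working it through.** **Inputs from the protocol (Statistical analysis):** about 36 per arm; difference 10, read as points on the 0–100% Oswestry scale; variability 15; two-sided 5%; power 80%; 1:1 allocation.

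**Assumed, because the protocol gives no figure:** the correlation rho between baseline and week 12, and equal variances at the two times. The value above 0.5 in the Outcomes section concerns Oswestry against Roland-Morris and cannot stand in for rho.

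**Step 1: reproduce the plan's figure.** By the normal approximation, n per arm = 2 × (1.960 + 0.842)² × 15² / 10² = 35.3, so 36. Power at 36 per arm is 80.7% by the normal approximation and 79.7% by the non-central t. The stated size is that of an unadjusted two-sample comparison with SD 15.

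**Step 2: compare the variances.** With a common SD s at both times:

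- change score: 2s²(1 − rho)
- ANCOVA: s²(1 − rho²)
- ratio, ANCOVA to change score: (1 + rho)/2

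**Step 3: power with 15 as the SD of change.** The effective SD under ANCOVA is 15 × √((1 + rho)/2). Power is by the non-central t, 36 per arm, 69 degrees of freedom; the unadjusted test has 79.7%.

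| rho | variance ratio | effective SD | power |
| --- | --- | --- | --- |
| 0.3 | 0.65 | 12.09 | 93.3% |
| 0.5 | 0.75 | 12.99 | 89.6% |
| 0.7 | 0.85 | 13.83 | 85.7% |
| 0.8 | 0.90 | 14.23 | 83.6% |
| 0.9 | 0.95 | 14.62 | 81.6% |

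At rho 0.5 and 0.7 the gain equals 1/0.75 − 1 = 33% and 1/0.85 − 1 = 18% more participants. A simulation of 4,000 trials with 36 per arm gave power of 80.1% for the t-test against 89.4% for ANCOVA at rho 0.5, and 79.6% against 85.0% at rho 0.7. Both methods estimated a mean difference of about −10.0.

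**Step 4: power with 15 as a within-patient SD.** The SD of change is 15 × √2 = 21.2. Unadjusted power at 36 per arm is 50.5%. ANCOVA gives 62.4% at rho 0.5 (SD 18.37) and 57.1% at rho 0.7 (SD 19.56).

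**Step 5: relax equal variances.** Let k be the week-12 SD divided by the baseline SD. The ratio becomes k²(1 − rho²)/(1 + k² − 2·rho·k). At k = 1.25 it is 0.89, 0.98 and 1.00 at rho 0.5, 0.7 and 0.8. It reaches 1 where rho × k, the true baseline slope, equals 1 (here 0.8 × 1.25).

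**Step 6: chance imbalance.** With 37 per arm, the standard error of the baseline difference is √(2/37) = 0.232 SD. A difference of at least 0.25 SD in either direction has probability of about 28%. At rho 0.5 and a baseline SD of 15, an imbalance of 0.25 SD shifts the change-score estimate by 0.5 × 0.25 × 15 = 1.9 points, against a target of 10.

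**The case against.** The strongest reply is that nothing here is an error. The t-test on change is a legitimate analysis, and with 15 read as the SD of change the plan meets roughly its own 80% target with its own test. An analysis plan that is not at hand may add adjusted analyses. All of this stands, and it makes the point an improvement to a valid plan. It does not remove the point, because the protocol itself names the between-group test.

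A reader might infer more than the documents support:

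- **That the baseline is wasted.** It is not. The change score uses every baseline value; only the slope is fixed instead of estimated.
- **That the planned result is biased.** Over randomisation it is not. The shift in the last step of the working is conditional on the imbalance that happens to occur, and it averages out.
- **That ANCOVA takes power from 80% to 90%.** That is one scenario: rho 0.5, equal variances, and 15 as the SD of change. The protocol states none of the three.
- **That any rho below 1 means over-correction.** This holds under equal variances. In general what matters is whether the true slope is below 1.
- **That within-arm tests are ranked equally with the between-group test, or will serve as evidence of efficacy.** The text gives each test its own purpose and says neither thing. What remains is that their descriptive role is not stated.

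**Conclusion.** The point holds as a free gain in precision, and no defect of validity is shown. The protocol fixes an unadjusted test where a baseline-adjusted one estimates the same mean difference and, in large samples, never has larger variance.

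Under equal variances the variance falls by 35% at rho 0.3 and by 5% at rho 0.9. With 15 as the SD of change, that is a rise in power at 36 per arm from about 80% to between about 93% and 82%. With 15 as a within-patient SD, it is a rise from about 51% to about 62% (rho 0.5) or 57% (rho 0.7). In that reading adjustment helps but does not bring the trial near 80%; what the 15% stands for is a separate question. The gain shrinks to nothing as the true baseline slope nears 1.

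**What to change.** In the Statistical analysis section, make the primary between-group analysis an ANCOVA with arm and the baseline value of the same measure as covariates, for Oswestry and SF-36. The response may be the week-12 score or the change; with baseline in the model the arm coefficient is the same. Report the adjusted difference with a 95% confidence interval.

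Use the same model for continuous secondary outcomes measured at baseline. Where baseline and week 12 are very highly correlated the gain will be small: at rho 0.98 the variance ratio is (1 + 0.98)/2 = 0.99.

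The change-score t-test may stay as a sensitivity analysis. State that within-arm changes are descriptive, preferably as means with confidence intervals, and are not used as evidence of a treatment effect.

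The cost is a change of wording and one residual degree of freedom (69 instead of 70 at 36 per arm). No new data or visits are needed, the sample size need not change, and the missing-data rule is unaffected. The change should be made before outcome data are seen, so that the model is not chosen after the fact.

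### T-tests on raw change in NSAID and paramedical use are valid but inefficient; baseline-adjusted regression of week-12 use would serve these two secondary outcomes better (low severity)

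*Protocol*

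**What the plan says.** The Outcomes section of the protocol lists among the secondary outcomes "use of non-steroidal anti-inflammatory Drugs (NSAIDS) and use paramedical interventions". It does not say whether use means dose, days, number of visits or yes/no, or over what window. On timing it says "All measures will be assessed at baseline, weeks 4, 8 and 12". The data come from a diary: "Both groups will also hand in the Pain Medication and Treatment diary chart, and exercise log at every visit".

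The Statistical analysis section opens its analysis paragraph with "All data will be analyzed according to intention to treat", then sets the summary measure, "We will calculate the mean change scores between groups at the specific weeks", and then the tests: "Paired t-tests will assess within group changes and two-sample t-tests will compare between groups". It exempts no outcome and names no other test. The sample size there concerns the primary outcome only: "a sample of about 36 in each group will be adequate to detect a 10% change in the primary outcome of self-reported pain". The inputs behind that figure are a variability of 15%, a 5% two-sided test and 80% power.

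**The concern.** The t-test on mean change suits a questionnaire score. Amounts of medication and numbers of visits behave differently. They are bounded at zero, and someone who uses nothing at baseline cannot improve. If most participants use little and a few use a lot, those few set the variance of the change score. Subtracting baseline in full, rather than adjusting for it, also adds noise.

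At stake is the precision of the two outcomes nearest to the question that motivates the trial. The Rationale cites escalating health plan costs, says that physiotherapy, chiropractic and massage made up 83% of paramedical services, and describes the trial as groundwork for a cost-effectiveness assessment.

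**Working it through.** **1. The plan's own figure.** With a difference of 10, an SD of 15, two-sided 5% and 80% power, n per group = 2 × (1.960 + 0.842)² × 15² / 10² = 2 × 7.85 × 2.25 = 35.3, rounded up to 36. The stated figure reproduces. It says nothing about NSAID or paramedical use, for which the protocol gives no figure.

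**2. Why change scores lose precision.** Let σ_b and σ_f be the SDs of baseline and follow-up use, and ρ their correlation. The variance of change is σ_b² + σ_f² − 2ρσ_bσ_f. The residual variance after regression on baseline is σ_f²(1 − ρ²). The first minus the second is (σ_b − ρσ_f)², which is never negative. Apart from the one degree of freedom spent on the baseline term, adjustment cannot do worse on this measure. This argument needs no assumption about skew.

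**3. Size under assumed distributions.** Assumed, not from the documents:
- Each participant's mean use is gamma distributed with shape k, and the baseline count is Poisson.
- The follow-up count is Poisson with further gamma (shape 2) variation.
- Treatment halves use.

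The arms have 37 and 38 participants, from the 75 in the Participants section. The share of zeros at baseline is (k/(k + μ))^k for mean μ.

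| Setting | Zeros at baseline | t-test on change | Week-12 use on arm and baseline use | Gain |
|---|---|---|---|---|
| NSAID amount, μ = 6 a week, k = 0.35 | (0.35/6.35)^0.35 = 36% | 39% | 48% | 9 points |
| NSAID amount, milder skew, μ = 6, k = 2 | (2/8)² = 6% | 68% | 78% | 10 points |
| Visits, μ = 1.5 per 4 weeks, k = 0.40 | (0.40/1.90)^0.40 = 54% | 26% | 33% | 7 points |

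**4. A second set-up.** This used 36 per group, 30/50/70% non-users, gamma-Poisson counts with mean 6 among users, and three effect patterns: all users halve their use; half of users stop; 60% continue at 60% of their use. Power of the t-test on change was 10-80%, and raw-scale baseline adjustment added about 4 to 24 points. Without a treatment effect the t-test rejected in 3.5-5.1% of trials and the baseline-adjusted regression in 3.7-5.4%, against a nominal 5%.

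**5. Heavy users.** In the second set-up the three most extreme of 36 participants in an arm supplied on average 55-88% of the squared deviation of change. In the two more skewed settings of step 3, the three most extreme of 38 controls supplied 68-74%.

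**6. If use is recorded as yes/no.** No heavy user can exist. In three assumed scenarios the t-test on change had 59, 78 and 83% power, against 67, 85 and 87% for baseline-adjusted linear regression: gains of 8, 7 and 4 points.

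**7. Does a log scale help further?** Not consistently.
- In step 3, regression of log(1 + use) on arm and log(1 + baseline use) reached 58, 79 and 39%, which is 10, 1 and 6 points above the raw-scale regression.
- In the second set-up it beat the raw-scale regression by 13 to 31 points when half of users stopped, but was lower in 8 of 9 scenarios when all users halved their use.
- Its exponentiated coefficient is a ratio of (1 + use) and depends on the unit. A true halving of visits reads about 0.91 if counted per week and 0.82 if counted per 4 weeks. A halving of NSAID amount reads about 0.72.

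**The case against.** The case for leaving the text alone has four parts.

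- **Scope.** The Statistical analysis section does not say that t-tests apply to every outcome, and its wording about change scores and a primary endpoint fits scale scores. A statistical analysis plan, not shown, may treat diary variables separately. This is fair as far as it goes. But the protocol does state a method, names no alternative and exempts nothing, so the point concerns stated text rather than an omission.
- **Validity.** Under randomisation the comparison of mean changes is unbiased for the difference in mean use, and the simulations show no inflated type I error. This stands in full. A reader might infer that the t-test is wrong for such data; neither the documents nor the simulations support that.
- **Distribution.** A reader might take it as established that these outcomes are skewed counts with many zeros. The protocol gives no unit, window, zero share or SD. Skew is plausible but assumed, and the yes/no version contradicts the heavy-user argument. This also stands.
- **Target.** Total cost follows the arithmetic mean, heavy users included. The planned mean difference addresses that; a log-scale ratio does not. This stands against replacing the scale, but not against adjusting for baseline on the raw scale, which keeps the mean difference.

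**Conclusion.** The point holds in a limited form. Taken literally, the protocol compares two diary-based use outcomes by a method that is valid but less efficient than one using the same data. In the settings with use halved, power was about 26-68% for the planned test and 33-78% with baseline adjustment, a gain of about 7 to 10 points. In the second set-up the gain was about 4 to 24 points. All these figures rest on assumed distributions, since none follows from the documents. They are for the ordinary regression test; a robust or bootstrap interval may give back part of the gain where skew is strongest.

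The tempting stronger claim, that a real halving of use would more often than not be missed, fails at the milder end, where the t-test had 68% power. Nor can the whole gain of a log-scale model over the t-test be put down to skew: with mild skew, 10 of the 11 points (68% to 79%) come from baseline adjustment.

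Both outcomes are secondary and were not used to size the trial. The primary conclusion is unaffected and the severity is low.

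**What to change.** For these two outcomes only, replace the t-test on change with the following:

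- Define the unit (amount of NSAID; number of paramedical visits) and one fixed diary window, the same in both arms. The treatment arm hands in diaries about twice a week and the control arm every two weeks, so totals per hand-in would not be comparable.
- Regress week-12 use on arm and baseline use. Report the adjusted mean difference with a robust or bootstrap 95% confidence interval, and the proportion with no use by arm.
- If only any/none is recorded, use a baseline-adjusted binary model reported as a risk difference.
- A log-scale analysis may be added as a sensitivity analysis, but its result must not be presented as a ratio of use.

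The cost is a few sentences. Baseline use is already collected in the diary, no new data are needed, and the planned tests for the other outcomes can stay. The effect is still read as a difference in mean use.
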